#### Intervention Delivery

Prior to the initiation of the intervention period, research staff will provide an intervention orientation to participants. This orientation, which will last approximately 30–60 min, will be completed either in-person or over video conference, and will include general sleep education as well as an explanation of the intervention components the participant will receive and the rationale behind them. After this orientation, participants will implement their assigned intervention components at home daily for 6 weeks.

The candidate intervention components will be administered *via* weekly emails. All participants will monitor their sleep by completing a daily sleep diary for the duration of the 6-week intervention period. All participants will also receive a weekly email from the study team with a reminder to complete and return the sleep diary. Sleep diaries will be returned electronically. For participants receiving stimulus control, the weekly email will also contain a reminder of the stimulus control instructions. For participants receiving systematic bright light exposure, the weekly email will also contain a reminder of how to use the Re-Timer™ glasses. For participants receiving sleep restriction, the weekly email will also contain a reminder of the sleep restriction instructions and the prescribed sleep schedule for the coming week, which will be determined by a licensed clinical psychologist with specialized training in behavioral sleep intervention ([name]) based on the prior week’s sleep diary. Participants receiving more than one candidate intervention component will receive a single weekly email containing the information relevant to all components being delivered. The study team will be available to participants throughout the intervention period to answer questions, troubleshoot, and provide support as needed.

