#### Covariates

##### Sociodemographic and Medical Information

Sociodemographic and medical information will be gathered through participant self-report and medical chart review at screening, baseline, post-intervention, and 3-month follow-up. Sociodemographic data will include age, education, income, racial background, ethnicity, employment status, and relationship status. Medical data will include information about exclusionary and comorbid medical conditions, prescription medication use, and cancer-related information (e.g., time since diagnosis, stage at diagnosis, treatment history). Participants will also complete the Self-Administered Comorbidity Questionnaire (Sangha et al., 2003).

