##### Pain

An 11-item numerical rating scale, ranging from 0 (*No pain*) to 10 (*Worst imaginable pain*), will evaluate pain intensity (Ferreira-Valente et al., 2011) at baseline, post-intervention, and 3-month follow-up. The numerical rating scale is one of the most commonly used measures of pain intensity and has been shown to be responsive to pain (Ferreira-Valente et al., 2011).

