##### Treatment Expectancy

Following the baseline assessment and orientation session and prior to the start of the 6-week intervention period, participants will complete the Credibility/Expectancy Questionnaire (Devilly and Borkovec, 2000). This six-item measure was developed for clinical studies to measure treatment expectancy and rationale credibility. It yields two subscale scores reflecting affectively based expectancy and cognitively based credibility.

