#### Part 2: Intervention Optimization

For Part 2, we will use benchmarks of 80% recruitment (i.e., 80% of eligible survivors) and 80% retention to demonstrate feasibility. We will use a benchmark of 60% protocol adherence for each candidate intervention component, based on prior studies of CBT-I and bright light in cancer survivors (Berger et al., 2003; Ancoli-Israel et al., 2012). Descriptive statistics will be applied to the FACIT-TS-G items to examine acceptability.

To identify the optimal combination of candidate intervention components, longitudinal mixed effects models will be fit to the data with primary and secondary outcomes evaluated in separate models. All study time points will be included in these models, and fixed effects will include time (a nominal variable with three levels, which will be entered as two indicator variables), each candidate intervention component, and two-way interactions among components. The effect of a component at post-intervention and 3-month follow-up will be assessed based on that component’s interaction with time. Candidate intervention components will be defined using effect coding (absence: −1, presence: +1) so effects remain uncorrelated (Kugler et al., 2012). Models will also adjust for hypothesized covariates as outlined above, as well as demographic and baseline clinical characteristics found to significantly differ across conditions. Further analyses will evaluate if the presence of multiple candidate intervention components has a greater effect on each outcome than single components. To do this, an additional variable will be created to indicate the number of components to which a participant was exposed (0, 1, 2, 3). This variable will be included as a fixed effect in these models, along with its interaction with time.

In addition to optimizing the intervention, we will also explore the potential mediating role of circadian markers (i.e., aMT6s, circadian activity rhythms, sleep regularity) on the effects of candidate intervention components. The potential mediating role of sleep disturbance on the relationships of intervention components to HRQOL and symptom burden will also be evaluated. Given the exploratory nature of this analysis, interpretation will focus on effect sizes rather than statistical significance.

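### Treatment expectancy, measured only after participants learn their assigned components, is an adjustment covariate in the main models, and pain and medication are not limited to baseline values

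*Protocol article*

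**What the plan says.** The Covariates part of the Measures section has four entries: sociodemographic and medical information (which includes prescription medication), sleep apnea risk, pain, and treatment expectancy. The analytic plan for Part 2 then states: "Models will also adjust for hypothesized covariates as outlined above", and adds a second set, "as well as demographic and baseline clinical characteristics found to significantly differ across conditions".

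The timing of each entry differs:

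- **Expectancy** (Treatment Expectancy): "Following the baseline assessment and orientation session and prior to the start of the 6-week intervention period, participants will complete the Credibility/Expectancy Questionnaire". The orientation (Intervention Delivery) includes "an explanation of the intervention components the participant will receive and the rationale behind them".
- **Pain** (Pain): the rating scale "will evaluate pain intensity (Ferreira-Valente et al., 2011) at baseline, post-intervention, and 3-month follow-up".
- **Sociodemographic and medical data, including medication** (Sociodemographic and Medical Information): "gathered through participant self-report and medical chart review at screening, baseline, post-intervention, and 3-month follow-up".
- **Sleep apnea risk** (Sleep Apnea Risk): baseline only.

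The models use all three assessments. Fixed effects are time, each component and the two-way interactions among components. A component's effect at post-intervention and at 3 months is read from its interaction with time.

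**The concern.** Randomisation balances what exists before assignment is known. A covariate measured afterwards can itself be moved by the assignment. Once it is in the model, the component coefficient is no longer the full randomised contrast: it is what remains after holding fixed a possible consequence of the component.

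Expectancy is exposed to this by design. In Table 1, condition 1 receives all three components and condition 8 receives none, and participants answer the expectancy questions after hearing what they will get and why. Expectancy could easily differ by component, or by the number of components. The plan chooses effect coding so that effects stay uncorrelated; a covariate that differs by component reintroduces correlation with the component terms.

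Part 2 decides which components count as active and are kept. If a component works partly through an adjusted variable, its estimate may be too small and it may be dropped. If an unmeasured factor drives both the covariate and the outcome, the bias can also run the other way.

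**Working it through.** **Step 1: which covariates can be affected by assignment, from the text alone.**

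| Covariate | When measured | Pre-assignment value exists? | Value entered in the model |
|---|---|---|---|
| Sleep apnea risk | Baseline | Yes | Baseline, the only one |
| Pain | Baseline, post-intervention, 3 months | Yes | Not stated |
| Medication | Screening, baseline, post-intervention, 3 months | Yes | Not stated |
| Expectancy | After baseline and orientation | No | Necessarily post-disclosure |

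In the adjustment sentence, the word baseline qualifies the second set (clinical characteristics found to differ across conditions), not the hypothesised covariates. Expectancy is therefore post-assignment on every reading; pain and medication are post-assignment on one reading only.

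**Step 2: the plan's own figure.** The only stated statistical figure is 80% power at effect size 0.40, two-sided alpha 0.05, with 40 against 40 per factor level. A plain two-mean comparison at 0.40 SD gives 43.2%. An unstated baseline correlation of about 0.77 with baseline adjustment (SD multiplied by √(1 − 0.77²)) gives 80.1%. The present point does not depend on this; 80% is taken as given below.

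**Step 3: how the form of adjustment matters.** The documents give neither a component effect on the covariate nor a covariate-outcome slope. Assumed: true component effect 0.40 SD; slope 0.3 SD of outcome per SD of covariate; the component shifts the covariate by a = 0.3 or 0.5 SD; no unmeasured common cause. The expected loss when the path is conditioned on is slope × a:

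- a = 0.3: 0.3 × 0.3 = 0.09 SD, and 0.09 / 0.40 = 22.5%.
- a = 0.5: 0.3 × 0.5 = 0.15 SD, and 0.15 / 0.40 = 37.5%.

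A simulated 2×2×2 trial (8,000 participants, three visits, random intercept, complete data) gave these component-by-post estimates:

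| Form of adjustment | a = 0.3: unadjusted → adjusted | a = 0.5: unadjusted → adjusted |
|---|---|---|
| Expectancy, time-constant main effect | 0.369 → 0.369 | 0.379 → 0.379 |
| Expectancy × time | 0.369 → 0.292 | 0.379 → 0.243 |
| Baseline pain only | 0.400 → 0.400 | 0.409 → 0.409 |
| Visit-level pain | 0.400 → 0.313 | 0.409 → 0.258 |

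Where the component did not shift the covariate, there was no material change (0.386 unadjusted; 0.382 with expectancy × time, 0.383 with visit-level pain).

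**Step 4: the terms without a time interaction.** Entered as a time-constant main effect, expectancy takes roughly its average slope over the three visits: (0 + 0.3 + 0.3) / 3 = 0.2. The component term then moves by 0.2 × 0.3 = 0.06 SD or 0.2 × 0.5 = 0.10 SD, although its baseline difference should be zero by randomisation. If two components together shift expectancy non-additively by 0.3 SD, the component-by-component term moves by the same 0.06 SD. A repeat simulation with 16,000 participants agreed: the component term went from -0.005 to -0.060 and from -0.005 to -0.109, and the component-by-component term from 0.072 to 0.010, while component-by-time did not move.

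**Step 5: what the loss would mean for power.** At 80% power the standardised effect is 1.960 + 0.842 = 2.802. Scaling by the remaining effect:

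- 0.31 / 0.40 × 2.802 = 2.171; power Φ(2.171 − 1.960) = 58%.
- 0.25 / 0.40 × 2.802 = 1.751; power Φ(1.751 − 1.960) = 42%.

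**The case against.** Three objections have weight.

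**Follow-up pain and medication.** A reader might infer that the models adjust for follow-up values. The documents do not say so. The two covariate sections give collection times, and repeat collection may simply follow from the later assessments mirroring the baseline one. The medical-information entry is a broad inventory that includes exclusionary conditions, so not all of it can be meant as an adjustment set, and the separate clause on characteristics that differ across conditions does say baseline. A condensed article may also leave the choice of visit to the full protocol or analysis plan. This objection stands: for pain and medication there is only an ambiguity to close.

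**Form of the expectancy term.** A reader might also infer that adjusting for expectancy necessarily removes part of the effects on which components are judged. It does not. The plan names time interactions where it wants them (components, number of components) and names none for covariates. On the natural reading expectancy is a main effect, and with complete data component-by-time is untouched. This stands too, but it does not rescue the covariate. The component and component-by-component terms still move, and the latter are listed without a time interaction.

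**Size.** The percentages come from chosen inputs. With no shift in the covariate the loss is zero, and an unmeasured common cause could reverse the direction. They are illustrations only.

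None of this alters the fact that expectancy is a listed adjustment covariate with no pre-assignment value.

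**Conclusion.** The point holds in a limited form. For expectancy it rests on the text: the plan adjusts for a variable measured after participants are told their components. That can bias the component and component-by-component terms, and the component-by-time effects if a time interaction is added. In the form that leaves component-by-time alone, it offers no gain for that contrast. For pain and medication the text is open, and entering visit-level values could bias component-by-time as well.

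The size cannot be fixed from the documents. Under the assumptions in the working (slope 0.3, covariate shift 0.3 to 0.5 SD, no unmeasured common cause), the loss is 0.09 to 0.15 SD of a 0.40 SD effect with an expectancy-by-time term or visit-level pain. It is zero for component-by-time with baseline pain only, or with an expectancy main effect and complete data. Because the effect on the deciding contrast depends on a model form the article does not state, this should be fixed but is not a fatal flaw.

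**What to change.** Two changes of wording in the Part 2 analytic plan, made before analysis:

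1. Take credibility/expectancy out of the adjustment set of the main models. Report it by condition, or use it in a sensitivity analysis or in the exploratory mediation analysis.
2. State that pain and medication enter as baseline values only. Follow-up values can be described by condition. Sleep apnea risk needs no change.

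All data are still collected and used. The sample size, visits and questionnaires do not change, so the only cost is the edit.

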## Abstract

Sleep difficulties, particularly symptoms of insomnia and circadian disruption, are among the primary complaints of gynecologic cancer survivors before, during, and after treatment. Moreover, difficulty sleeping has been linked to poorer health-related quality of life and elevated symptom burden in this population. Although leading behavioral sleep interventions have demonstrated efficacy among cancer survivors, up to 50% of survivors are non-adherent to these treatments, likely because these interventions require labor-intensive behavior and lifestyle changes. Therefore, there is a need for more effective and acceptable approaches to diminish sleep disturbance among cancer survivors. This manuscript describes the methodology of a two-part study guided by the Multiphase Optimization Strategy (MOST) framework to identify a streamlined behavioral sleep intervention for gynecologic cancer survivors. Three candidate intervention components previously shown to decrease sleep disturbance will be evaluated, including sleep restriction, stimulus control, and systematic bright light exposure. Participants will be adult women with a history of non-metastatic gynecologic cancer who have completed primary treatment and who report current poor sleep quality. Fifteen participants will be recruited for Part 1 of the study, which will utilize qualitative methods to identify barriers to and facilitators of intervention adherence. Results will inform changes to the delivery of the candidate intervention components to promote adherence in Part 2, where 80 participants will be recruited and randomized to one of eight conditions reflecting every possible combination of the three candidate intervention components in a full factorial design. Participants will complete assessments at baseline, post-intervention, and 3-months post-intervention. Part 2 results will identify the combination of candidate intervention components that yields the most efficacious yet efficient 6-week intervention for diminishing sleep disturbance. This is the first known study to apply the MOST framework to optimize a behavioral sleep intervention and will yield a resource-efficient treatment to diminish sleep disturbance, improve health-related quality of life, and decrease symptom burden among gynecologic cancer survivors. ClinicalTrials.gov Identifier: NCT05044975.

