### Study Design

This two-part study is guided by the MOST framework. Participants in Part 1 will not be randomized, but rather will receive all three candidate intervention components simultaneously. It is well established that greater adherence predicts behavioral sleep intervention efficacy; however, knowledge of how best to increase adherence is limited (Matthews et al., 2012, 2013; Agnew et al., 2021). Therefore, upon completion of the intervention in Part 1, individual semi-structured interviews will be conducted with participants and analyzed to identify barriers to and facilitators of adherence to the three candidate intervention components. Results will inform the design and delivery of the components in Part 2 to enhance adherence. Subsequently, in Part 2, a full factorial experiment will be completed that involves eight experimental conditions (Table 1). It is important to note that this study is not an eight-arm RCT and the purpose is not to compare outcomes across each of the eight conditions directly. Rather, each main effect and interaction estimate will use data from participants in all of the experimental conditions. For example, the main effect of sleep restriction will be estimated by comparing the mean for the 40 participants in conditions 1 through 4 to the mean for the 40 participants in conditions 5 through 8 in Table 1. A detailed explanation of how factorial study designs maintain power has been previously published (Collins et al., 2009).

**TABLE 1 T1:** Experimental conditions.

Experimental condition	Sleep restriction	Stimulus control	Bright light
1	Yes	Yes	Yes
2	Yes	Yes	No
3	Yes	No	Yes
4	Yes	No	No
5	No	Yes	Yes
6	No	Yes	No
7	No	No	Yes
8	No	No	No

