### Hypotheses

We hypothesize that gynecologic cancer survivors will be able to engage with each of the three candidate intervention components and that each component will be deemed acceptable. We further hypothesize that the optimal combination of intervention components will yield stronger effects for diminishing sleep disturbance, improving HRQOL, and reducing symptom burden than each individual component.

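### The 0-1-2-3 component count cannot show that a combination beats its own single components, whichever way it is fitted

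*Protocol article*

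**What the plan says.** The Abstract describes a full factorial: "80 participants will be recruited and randomized to one of eight conditions reflecting every possible combination of the three candidate intervention components". Under Part 2: Intervention Optimization, the mixed models contain time, "each candidate intervention component, and two-way interactions among components". The coding is fixed: "Candidate intervention components will be defined using effect coding (absence: −1, presence: +1) so effects remain uncorrelated". A component's effect at each follow-up "will be assessed based on that component’s interaction with time".

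The same section then asks whether receiving multiple components has a greater effect on each outcome than receiving single ones. The method it gives is that "an additional variable will be created to indicate the number of components to which a participant was exposed (0, 1, 2, 3", and "This variable will be included as a fixed effect in these models, along with its interaction with time". It does not say that the component terms are removed, or whether the count is numeric or nominal. The section's exploratory label comes later and is attached to the mediation analyses.

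The related hypothesis, under Hypotheses, is that the "optimal combination of intervention components will yield stronger effects for diminishing sleep disturbance" (and for quality of life and symptom burden) compared with each component by itself.

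**The concern.** The count is built entirely from the three component codes, so it holds no information that the factorial model lacks. What it does hold is a total that ignores which components were received. The question of whether a combination beats its constituents depends on exactly that identity: does adding bright light to sleep restriction, for example, gain anything over sleep restriction alone?

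At stake is the multiple-versus-single conclusion. The trial could report that more components are better when the added components contribute nothing, or it could obtain no estimate at all. In either case the stated hypothesis about the optimal combination would have no valid test, and the section names no other analysis for the multiple-versus-single question.

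**Working it through.** **Inputs.** 80 participants and eight conditions (Abstract). Each main effect compares 40 with 40; Study Design speaks of "the mean for the 40 participants in conditions 1 through 4". Codes are −1/+1 (Part 2: Intervention Optimization). Ten per condition is inferred from these figures, giving 10, 30, 30 and 10 participants at counts 0, 1, 2 and 3. Assumed for the probabilities and standard errors: one time point, outcome SD 1, no baseline adjustment, two-sided 5% test.

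**The plan's own figure.** None is given for the count analysis. The 80% power at effect size 0.40 concerns main effects and two-way interactions, and nothing below depends on it.

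**1. Numeric count added to the factorial models.** With SR, SC and BL the −1/+1 codes for sleep restriction, stimulus control and bright light:

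- count = 1.5 + 0.5 × (SR + SC + BL), exactly. Condition 1: 1.5 + 0.5 × 3 = 3. Condition 8: 1.5 − 0.5 × 3 = 0.
- Intercept, three main effects and three two-way terms: 7 columns, rank 7. With the count: 8 columns, rank still 7.
- Three time points with component-by-time terms: 15 columns, rank 15. With the count and count-by-time: 18 columns, rank still 15.
- With two-way-by-time terms as well: 21 columns, rank 21. With the count and count-by-time: 24 columns, rank still 21.

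Neither the count nor its time interaction can be estimated.

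**2. Nominal count added to the factorial models.** Three indicators make 10 columns, rank 8. The one added degree of freedom is the three-way interaction: what is left of each indicator after the factorial terms is perfectly correlated (±1) with SR × SC × BL. That is not a comparison of multiple with single.

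**3. Count fitted in separate models.** In the balanced design the least-squares slope is the average of the three main effects. Suppose one component has effect d and the other two have none:

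- Expected means at counts 0, 1, 2, 3: 0, d/3, 2d/3, d.
- Slope: (d + 0 + 0)/3 = d/3 per component.
- Two or more minus one: (30 × 2d/3 + 10 × d)/40 − d/3 = 0.75d − 0.333d = 0.417d. A nominal count fitted alone gives the same figure for this comparison.
- True gain from adding an inert component to the active one: 0.

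At d = 0.6 SD the means are 0, 0.2, 0.4 and 0.6, the slope is 0.2, and two-or-more minus one is 0.417 × 0.6 = 0.25 SD.

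Simulated chance of a significant positive slope:

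| Effect of the one active component | Chance |
|---|---|
| 0.4 SD | about 17% |
| 0.6 SD | about 31% |
| 0.8 SD | about 49% |

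If instead any one component is enough and further ones add nothing (means 0, d, d, d), the slope is still 0.25d.

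**4. Contrasts that do answer the question.** In the main-effects and two-way model, each coefficient has variance 1/80.

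- Two components versus one of them: twice the sum of three coefficients (up to sign), so SE = 2 × √(3/80) = 0.387 SD.
- Three versus one: twice the sum of four coefficients (up to sign), so SE = 2 × √(4/80) = 0.447 SD.
- Power for a 0.40 SD difference: roughly 18% and 14%.

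**The case against.** The strongest reply is that the count comes after the optimisation decision and does not drive it. The plan chooses components from the factorial models, each judged by its own interaction with time. If only sleep restriction worked, the estimates for the other two would centre on zero and show this. That stands. A reader might infer that the count would lead the trial to keep inert components, against its aim of an intervention made only of active ones. The article does not support this: nowhere does it give the count a role in selection, and the factorial effects are unaffected as long as they are read from models without the count.

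A second reply is that non-estimability and a misleading slope cannot both occur. This also stands. They are alternatives that depend on which models the sentence means, and the wording allows either.

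A third is that the multiple-versus-single question can be read as an average over cells, which a nominal count fitted alone does estimate. With one active component the combination cells really are better on average, because more of them contain it. But that average does not tell whether a combination beats its own constituents, and the hypothesis is stated against each individual component.

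A fourth is that coding and exact contrasts are commonly left to the analysis plan. That would answer a complaint of missing detail. Here the article prescribes a method, and every reading of it fails the constituent comparison.

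**Conclusion.** The point holds, within limits. The prescribed count cannot show that a combination outperforms its constituent single components: it is aliased, reduced to the three-way term, or turned into an average of main effects that is positive when a single component works. The rank results and expected slopes need only the balanced allocation. The 17%, 31% and 49% also rest on one time point, SD 1 and no baseline adjustment. At 0.40, the only effect size the plan names, the applicable figure is 17%; 0.6 and 0.8 SD are illustrations.

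The damage is confined to the multiple-versus-single conclusion and the hypothesis about the optimal combination. The main effects, the two-way interactions and the choice of components do not depend on it.

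**What to change.** Replace the sentences on the count with contrasts of the selected combination minus each of its single components, at post-intervention and at 3 months, with confidence intervals. Take them from the factorial model extended with component-by-component-by-time terms; the article lists two-way interactions and component-by-time effects but not these three-factor terms, so they must be added. Label the contrasts exploratory, because the combination is chosen on the same data, and leave confirmation to the later randomised trial that the Discussion foresees.

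If the count is kept, fit it in a separate model without the component terms, call it descriptive, and state that it does not inform component selection.

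The cost is a few sentences and some added model terms, with no change to design, sample size or data collection. The drawback is imprecision: with the standard errors and power above, the contrasts should be read as estimates with intervals and not as tests.

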## Materials and Methods

### Participants and Recruitment

Across both parts of the study, participants will be survivors of a non-metastatic gynecologic cancer who have completed primary treatment, are between the ages of 18 and 74, and report poor sleep quality. Part 1 of the study will include 15 participants and Part 2 will include 80, for a total sample size of 95 participants to be enrolled over 5 years. Participants will be recruited from the Robert H. Lurie Comprehensive Cancer Center of Northwestern University and the University of Arizona Cancer Center, two comprehensive cancer centers located in Chicago, IL and Tucson, AZ, United States, respectively. All potential participants will provide verbal consent to complete screening for study eligibility. Those who are eligible and subsequently enroll will provide written informed consent prior to engaging in any study activities.

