Power analyses for Part 2 were conducted using the Factorial Power Plan Macro for SAS (Dziak et al., 2013) to detect an effect size ≥0.40 for main effects and two-way interactions with 80% power and two-sided alpha = 0.05. Analyses will be conducted using a maximum likelihood estimation approach, which provides valid inference in the presence of missing data under a missing at random assumption (Enders and Bandalos, 2001). Once all data are collected, they will be imported into SPSS (IBM, Armonk, NY, United States) (IBM Corp, 2020) for cleaning. Data will then be analyzed in SPSS (IBM Corp, 2020), and MPlus (Muthén & Muthén, Los Angeles, CA, United States) (Muthén and Muthén, 1998-2017).

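### The stated 80% power for an effect size of 0.40 cannot be reproduced from 80 participants: read as a mean difference it is about 42%, and reaching 80% needs an unstated correlation near 0.8 or a different effect-size metric

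*Protocol article*

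**What the plan says.** All references are to the protocol article.

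- **Sample size** (Participants and Recruitment): "Part 1 of the study will include 15 participants and Part 2 will include 80".
- **Power** (Analytic Plan, Part 2: Intervention Optimization): the power analysis used a SAS macro for factorial designs and was run "to detect an effect size ≥0.40 for main effects and two-way interactions with 80% power and two-sided alpha = 0.05". The section does not define the effect-size metric and gives no baseline-to-follow-up correlation, attrition allowance or macro settings.
- **Main effects** (Study Design): the main effect of sleep restriction is illustrated as "comparing the mean for the 40 participants in conditions 1 through 4 to the mean for the 40 participants in conditions 5 through 8".
- **Analysis model** (Part 2: Intervention Optimization): a longitudinal mixed model, in which "All study time points will be included in these models". A component's effect at each follow-up is judged by its interaction with time. Components are coded −1 and +1.
- **Retention** (same section): "80% retention to demonstrate feasibility". This is a feasibility benchmark; it is not given as an input to the power analysis.
- **Missing data** (same section): maximum likelihood, assuming data are missing at random.

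**The concern.** A reader who sees an effect size of 0.40 next to a comparison of two group means will take it as a standardised difference. On that reading, 40 against 40 falls far short of 80% power. The factorial layout does not help further, because 40 against 40 already uses all 80 participants.

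The stated power tells readers how much weight a null result for a component can bear. The Discussion says that the final treatment will contain only active components. If the design is sensitive only to differences well above 0.40, a component with a real effect of that size could easily show no clear effect, and the printed 80% would give false reassurance about that result.

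**Working it through.** **Inputs from the article:** N = 80 (40 against 40), effect size 0.40, two-sided alpha 0.05, stated power 80%.

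**Assumptions, not in the article:** the baseline-to-follow-up correlation r, shown over a range; equal variances at each time point; 64 completers (0.80 × 80) as a complete-case scenario.

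**Formula.** For a standardised difference d between two halves of N participants, the noncentrality is d × √(N/4) / √v, referred to a noncentral t. The variance factor v is 1 with no baseline gain, 2(1 − r) for a change contrast, and 1 − r² with baseline adjustment. Residual degrees of freedom are 78 for a plain t test and 72 to 73 for the factorial model; the choice barely matters.

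**1. Attempt to reproduce the stated 80%, with d = 0.40 and v = 1.** Noncentrality = 0.40 × √20 = 1.79, against a critical value of 1.99. Power is 42.4% (42.3% with factorial-model degrees of freedom, 43.2% by the normal approximation). The 80% is not reproduced. By the normal approximation, 80% power needs 99 per level, or 198 in total. Relaxing alpha to one-sided 0.05 or two-sided 0.10 gives only about 55%.

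**2. Using baseline, d = 0.40.**

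| r (assumed) | Change, N = 80 | Adjusted, N = 80 | Change, 64 complete | Adjusted, 64 complete |
|---|---|---|---|---|
| 0.5 | 42.3% | 53.1% | 34.9% | 44.3% |
| 0.6 | 50.5% | 59.7% | 42.0% | 50.2% |
| 0.7 | 62.5% | 69.5% | 52.8% | 59.6% |
| 0.8 | 79.7% | 83.7% | 70.1% | 74.6% |
| r needed for 80% | 0.80 | 0.78 | 0.84 | 0.83 |

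Example: change contrast at r = 0.8, v = 0.4, noncentrality = 1.789 / √0.4 = 2.83, power 79.7%. The component-by-time test in the plan corresponds to the change columns. Averaging both follow-ups with baseline adjustment would lower the required r to about 0.66 with 80 participants, but the plan assesses each follow-up separately.

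**3. Reading 0.40 as an effect-coded coefficient.** With −1/+1 coding, the difference between levels is 2 × 0.40 = 0.80. With v = 1, noncentrality = 0.80 × √20 = 3.58 and power is 94.2%. With 64 completers it is 0.80 × √16 = 3.20 and 88.3%.

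**4. Detectable difference at 80% power.**

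| | No baseline gain | Adjusted, r = 0.5 (assumed) |
|---|---|---|
| N = 80 | 0.63 | 0.635 × √0.75 = 0.55 |
| 64 complete | 0.71 | 0.712 × √0.75 = 0.62 |

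**5. Two-way interactions.** On the effect-coded scale an interaction has the same power as a main effect, 42.3% at 0.40 with v = 1. If 0.40 meant an unhalved difference between simple effects, the equivalent d would be 0.20 and power about 14%.

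**The case against.** The strongest reply is that the article does not say 0.40 is a mean difference. It effect-codes the components, and a coefficient of 0.40 on that coding gives 94%, which meets the 80% claim. With the planned change contrast, a difference of 0.80 gives 82% with 64 completers at an assumed r of 0.4, and 76% at r of 0.3, so this reading can even land close to 80%. This stands: the coefficient reading cannot be excluded, and it supports the claim if it was intended. It would also mean that the study is sized for differences twice as large as most readers would take from the text.

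It is also fair that the 40-against-40 comparison illustrates how a factorial design pools conditions and is not the planned test, which uses baseline. The 42% is therefore the bottom of the range for r of 0.5 to 0.8.

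Four stronger conclusions are tempting, and the article does not support them:

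- **That true power is near 40%.** This needs 0.40 to be a mean difference and baseline to contribute little. Neither is stated.
- **That dropout will cut the sample to 64.** The retention figure is a feasibility benchmark, and maximum likelihood also uses partial data. The 64-completer columns are a scenario.
- **That interactions have only 14% power.** This needs a scale that the article does not use.
- **That components will be discarded for non-significance.** No such rule is printed.

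An article may leave macro settings to the full protocol. That does not settle the matter, because the article prints a specific power figure next to a design that does not yield it on the plain reading.

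**Conclusion.** The point holds in conditional form: the stated 80% power for 0.40 does not follow from the printed sample size, comparison and alpha. As a standardised mean difference, power is about 42% without baseline gain, and 42% to 80% (change contrast) or 53% to 84% (baseline adjusted) for assumed correlations of 0.5 to 0.8.

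The claim is met in only two ways, both resting on something unstated. One is a correlation of about 0.78 to 0.80 with no dropout, or 0.83 to 0.84 if only 64 complete. The other is a metric in which 0.40 means a difference of 0.80 (94%, or 88% with 64 completers, both without baseline gain). The article does not show which, if either, was intended, so the finding is that the claim is unsupported as printed; it is not proof that the design is underpowered. The interaction scale and attrition are secondary.

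**What to change.** Restate the power sentence with three inputs, and correct the figure to match them:

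1. The effect-size metric: standardised mean difference or effect-coded coefficient. If it is a coefficient, say that 0.40 is a difference of 0.80 between levels.
2. The assumed baseline-to-follow-up correlation, with its basis.
3. The number assumed to be retained.

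If 0.40 is a mean difference and no strong correlation can be justified, state that 80 participants give 80% power for a difference of about 0.63 without baseline gain, or about 0.55 with baseline adjustment at an assumed correlation of 0.5. If 64 complete, the figures are about 0.71 and 0.62. Also state that the interaction effect size is on the effect-coded scale.

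The cost is wording and a rerun of the power calculation. No extra participants are needed. Unless the coefficient reading or a high correlation was intended, the stated figure becomes less favourable.
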